### Intervention

The intervention to be tested is the MyBraincoach-app, which was developed and evaluated at the Alzheimer Centre Limburg, Mental Health and Neuroscience Research Institute at Maastricht University (Maastricht, the Netherlands) under the name ‘MijnBreincoach’. The app aims to improve knowledge of brain health and motivation for behaviour change in the general population through tailored lifestyle advice. It has been approved as an evidence-based tool by the Dutch municipal health services and the Ministry of Health, Welfare and Sport.

The central component and scientific basis of the app is the LIfestyle for BRAin Health (LIBRA)-score,^31^ capturing an individual’s potential for dementia risk reduction. It has been developed by researchers at Maastricht University, based on a systematic review and Delphi consensus study. LIBRA is a comprehensive modifiable dementia risk score, which has been extensively validated as a predictor of cognitive decline, incident dementia and biomarkers of brain health.^32–35^ Originally, LIBRA comprised 12 modifiable risk/protective factors for dementia, that is, diabetes mellitus, hypercholesterolaemia, chronic kidney disease, heart disease, obesity, hypertension, depression, physical inactivity, healthy diet, high alcohol consumption, smoking and high cognitive activity. Each factor is assigned a weight, based on the relative risk of said factor,^31^ resulting in a LIBRA-score ranging from −5.9 to +12.7 points. Higher scores indicate higher risk for dementia or more room for improvement through lifestyle modification. Following an update in 2024, based on an umbrella review of systematic reviews and a Delphi consensus study, three new risk factors were added, that is, sleep disturbances, low social contact and hearing impairment,^36^ with scores of the updated LIBRA ranging from −6.1 to 25.7 points. Respective app modules targeting said factors have been developed and implemented in the Dutch original version of the app at Maastricht University.

Participants will be advised to use the app independently on a daily basis for 12 consecutive weeks. Use of the app comprises the following steps:

Completion of the LIBRA-assessment to identify present/absent risk factors for dementia (LIBRA profile), based on n=15 modifiable risk/protective factors for dementia. The LIBRA profile comprises three parts: ‘keep this up’, that is, sum of risk factors absent for the individual; ‘remember to manage well’, that is, sum of risk factors which are not directly amendable to change, for example, diabetes mellitus, but should be monitored regularly, for example, during usual visits to the attending GP; ‘room for improvement’, that is, sum of risk factors present for the individual and modifiable through lifestyle change. Preferably, participants will select a factor indicating room for improvement. However, participants with limited or no room for improvement may freely choose any lifestyle factor or health condition covered by the app.Choosing a lifestyle factor/condition to address, preferably among lifestyle factors indicating room for improvement. Users can change their risk factor of interest any time.Receipt of daily notifications for 14 consecutive days on the chosen lifestyle factor/condition; if a notification is not opened, its content is stored until the next day, that is, users can engage with a topic for more than 14 days if not all notifications are opened on a daily basis.Choice of a new lifestyle factor/condition to address.

The MyBraincoach app is designed to support users in behaviour change for dementia risk reduction by providing tailored advice based on participants’ individual risk profile, using micro-teaching (2–5 min reading time) notifications sent to users’ smartphones. Notifications can contain educational material, quizzes, personalised tasks/challenges, for example, setting specific goals for the chosen behaviour. The intervention is based on the theory of planned behaviour,^37^ which has shown very good predictive qualities for health behaviour change, control beliefs and attitudes in studies on prevention and public health approaches.^38^ Following this theory, an intention to perform specific behaviours is a function of the underlying attitudes toward the behaviour, subjective norms and perceived behaviour control. The respective app modules aim to positively influence attitudes and control beliefs towards behaviour change (eg, increased physical activity, smoking cessation) to evoke small steps for lifestyle changes beneficial for brain health by providing personalised feedback on modifiable risk and protective factors for dementia. In a study testing the Dutch version of the app, users evaluated MyBraincoach positively, with 75.5% stating that they enjoyed using the app, and 80.4% indicating that the app improved their understanding of the concept of brain health.^29^ Further, in a proof-of-concept study in Dutch primary care patients, 69.2% of users considered the app useful, and the app improved participants’ knowledge on dementia risk reduction. Dementia risk, assessed using the LIBRA-score, improved in both the intervention (GP consultation+app) and control group (GP consultation only^28^).

Uptake and use of eHealth tools is often lower in individuals with lower levels of education.^39
40^ Therefore, we will conduct usability testing sessions, including individuals with varying degrees of education to ensure usability across different educational backgrounds prior to the pilot study. Research on eHealth use, specifically for health promotion and prevention, in people with disabilities is currently scarce. Single studies identified higher perceived difficulty and overall lower eHealth use in people with disabilities than in non-disabled controls.^41^ To increase accessibility, app contents will be checked against the Web Content Accessibility Guidelines. The app will be tested for readability with a screen reader and usability testing sessions with individuals with visual impairment will be conducted prior to the pilot study. Usability testers (n=6) will be recruited using convenience sampling (eg, advertisements at community centres, religious/cultural organisations, health and social services, social media channels of Leipzig University, personal networks) and will be invited to test the app during a testing session (scheduled duration: ca. 90 min) at Leipzig University. Participants will report their experience with use of the app directly to a member of the research team.

### Outcomes and measures

As this pilot study is not designed to assess intervention effectiveness, no single primary endpoint was specified. The primary objective is to assess the feasibility and acceptability of the adapted MyBraincoach app and the associated study procedures. No single primary endpoint was specified, as the study is not designed to assess intervention effectiveness. Key feasibility outcomes include feasibility of recruitment, success rate of retention of participants at 12 weeks follow-up, app use, perceived usefulness and usability of the app, as well as reasons for dropout in participants who will have discontinued participation (assessed via email).

As exploratory outcomes, we will assess knowledge of risk and protective factors for dementia (dementia literacy), change in dementia risk profiles (risk/protective factors exhibited by participants), perceived barriers towards and motivation for behaviour change. Changes in dementia risk profiles are expected primarily in behavioural and symptom-related components of the LIBRA-score, including nutrition, physical activity, alcohol consumption, smoking, cognitive and social activity, sleep and depressive symptoms. Chronic conditions like, for example, diabetes or coronary heart disease are not expected to resolve during the 12-week intervention and will be used primarily to characterise participants’ risk profiles. The same instruments will be administered both at baseline and follow-up to assess changes in the LIBRA-score and its individual components, based on participants’ self-report. A full description of outcomes and respective assessments applied is given in table 1.

**Table 1 T1:** Outcomes and assessments to be used in the course of the pilot study

Construct	Instrument	BL	FU
Key feasibility outcomes			
Success and feasibility of recruitment	Information on: numbers of individuals (1) interested in the study, (2) signed informed consent, (3) eligible for participation; time necessary for recruitment; response to each recruitment channel; diversity of participants; time and resources spent on different recruitment channels; time from initial contact to enrolment, collected at study centre, standardised forms	x	
Retention rate	Rate of participants completing the follow-up assessment		x
App use	Meta-data on (1) downloads of the app, (2) interactions with the app, (3) app modules used, (4) topics chosen to address, (5) number of notifications received		x
Usability	German mHealth App Usability Questionnaire – Short Version (G-MAUQ^44^)		x
Usefulness	Technology Acceptance Model Questionnaire (TAM^45^)		x
Non-use of the app, dropout	Standardised questions on reasons for non-use of the app or leaving the study in participants who will have dropped out		x
Exploratory outcomes			
Changes in dementia risk profile	LIBRA-score, comprising information on: *Nutrition*: Mediterranean Diet Adherence Screener (MEDAS^46^); Dietary Fat and Free Sugar – Short Questionnaire (DFS^47^) *Physical activity*: International Physical Activity Questionnaire (IPAQ^48^) *Cognitive activity*: ‘Leisure Time’-scale of the Cognitive Reserve Index Questionnaire (CRIq^49^) *Alcohol consumption, smoking*: standardised questionnaire^50^ Hypercholesterolaemia, diabetes, hypertension, obesity, coronary heart disease, chronic kidney disease: standardised questionnaire^51^ *Depression*: Patient Health Questionnaire (PHQ-9^52^) *Social activity*: Lubben Social Network Scale (LSNS-6^53^); loneliness (UCLA Loneliness Scale^54^) *Hearing impairment*: Mini-Audio-Test (MAT^55^); possession and use of hearing aids *Sleep*: Athens Insomnia Scale for non-clinical application (AIS-NCA^56^)	x	x
Dementia literacy	Standardised questionnaire on knowledge of modifiable risk factors for dementia^19 20^	x	x
Health-related quality of life	EuroQol Visual Analogue Scale (EQ-VAS^57^)	x	x
Self-efficacy	General self-efficacy^58^; domain-specific self-efficacy (LIBRA-factors nutrition, physical activity, social activity, cognitive activity, smoking cessation, alcohol consumption^59^)	x	x
Motivation for behaviour change	Standardised questionnaire, as applied in Zülke *et al*^60^; reason for participation (standardised forms)	x	x
Sociodemographics	Standardised questionnaire (age, sex, education, occupational status, living situation, marital status)	x	

BL, baseline; FU, follow-up; LIBRA, LIfestyle for BRAin Health.

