Against this background, we aim to test a translated and adapted version of an evidence-based mHealth intervention for dementia risk reduction, the MyBraincoach-app,^29^ in a pre-post pilot study among German adults aged 40–75 years. Feasibility and acceptability will be evaluated in terms of:

Feasibility of recruitment.Success rate of retention of participants at 12 weeks follow-up assessment.Usage (patterns) of the app.Perceived use and usability of the app.Reasons for non-use and study dropout.

Further exploratory objectives are:

To investigate change in knowledge of risk and protective factors for dementia.To describe changes in dementia risk profiles at 12 weeks follow-up.To assess changes in self-efficacy, motivation for behaviour change and health-related quality of life.To gain exploratory insights into participants’ perception of the app by means of a moderated focus group.

A proof-of-concept-study in community-dwelling middle-aged adults in the Netherlands investigated usage patterns and appreciation of the Dutch app (V.1.0), as well as changes in knowledge and attitudes towards dementia risk reduction.^29^ While overall app use was modest (56%), those who used the app evaluated it positively, increased their knowledge on dementia risk reduction and showed more positive beliefs about health behaviour change at follow-up. In a further proof-of-concept-study testing the app in Dutch primary care patients (n=188), 69.2% of users considered the app useful.^28^ The app improved knowledge on dementia risk reduction, while dementia risk improved in both the intervention (GP consultation+app) and control group (GP consultation only).

The present study aims to provide context-specific evidence on recruitment and retention, patterns of app engagement, perceived usefulness and usability and accessibility of an adapted version of the app in a German setting. By combining a quantitative feasibility assessment with qualitative user feedback, it will provide implementation knowledge required to refine the intervention and inform the design of a subsequent RCT.

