### Study procedures

After signing the informed consent form, participants will complete the baseline assessment, comprising standardised questionnaires on sociodemographic factors, health-related quality of life, self-efficacy, motivation for behaviour change and knowledge about risk/protective factors for dementia (see ‘Outcomes and measures’ section). A reminder will be sent per email to those having consented but did not complete the baseline assessment after 2 weeks. If no baseline data are submitted after this reminder, only the signed consent and minimal contact information will be retained for documentation purposes, and no other personal data will be processed. Consenting participants will then be able to download the MyBraincoach-app. All participants will receive a reminder via email 2 weeks after enrolment in the study to encourage download and use of the app.

At the end of the intervention period (12 weeks), all participants will receive an email with a link to the follow-up assessment, containing the same questionnaires as used at baseline, as well as assessing perceived use and usability of the app. During the follow-up assessment, participants can provide consent to be re-contacted for participation in the video-based focus group. A remote focus group with an expected duration of 90–120 min will then be scheduled, including n=8 pilot study participants, moderated by a researcher experienced in qualitative methodology. Participants will be purposively selected from those consenting to be re-contacted. Subject to participant availability, selection will aim to include individuals with different levels of app engagement, varied educational and sex backgrounds.

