### Sample size

As our study is a pilot study applying a pre-post design, a power analysis to determine sample size was not indicated. To assess use and usefulness of the MyBraincoach app, a sample size of n=75 is deemed sufficient to obtain data of n=60 participants for analyses at follow-up, expecting a dropout rate of 20%.

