### Data analysis plan

#### Quantitative analyses

All acquired data will be examined for potential inconsistencies and missing values. Drop-out analyses will assess potential systematic biases between participants who complete the follow-up assessment 12 weeks after baseline and non-completers, using χ² and two-sample t-tests, as appropriate. Success and feasibility of recruitment, retention of participants, use and usability of the app as well as reasons for dropouts will be described using means (SDs) and percentages, as appropriate. Changes in LIBRA, dementia literacy, health-related quality of life, self-efficacy and motivation for behaviour change will be described using dependent samples t-tests. The significance level of all analyses will be set to p<0.05 (two-tailed). Analyses will be conducted using Stata/SE V.16.0. Results will be reported according to the extended guidelines of the CONSORT statement for pilot and feasibility trials.^30^

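### Reasons for not using the app are a stated objective, but as most naturally read the plan puts the question only to dropouts, so retained non-users may never be asked why

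*Protocol article*

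**What the plan says.** The Introduction of the protocol article gives as one of its five feasibility and acceptability aims: "Reasons for non-use and study dropout". Four later places bear on how this is measured.

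- **Table 1** (Outcomes and measures), in the row for non-use and dropout, marked at follow-up: "Standardised questions on reasons for non-use of the app or leaving the study in participants who will have dropped out".
- **Text of Outcomes and measures**, in the list of key feasibility outcomes: "reasons for dropout in participants who will have discontinued participation (assessed via email". Reasons for non-use are not named. The same section refers the reader to Table 1 for the full account of outcomes and assessments.
- **Study procedures**, on the 12-week survey sent to all participants: "containing the same questionnaires as used at baseline, as well as assessing perceived use and usability of the app". No item on reasons for non-use is listed.
- **Quantitative analyses**: "use and usability of the app as well as reasons for dropouts will be described using means (SDs) and percentages". Again only dropout reasons are named.

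App use itself is recorded for participants through "Meta-data on (1) downloads of the app, (2) interactions with the app, (3) app modules used" and related counts.

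**The concern.** Not using the app and leaving the study are different events. A participant can fill in the 12-week questionnaire without ever having opened the app, or after giving it up in week 2. Metadata will show that this happened but not why.

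If the non-use questions go only to people who dropped out, the reasons obtained come from a subset of non-users, namely those who also left and who answer an email. Their reasons for not using the app may differ from those of people who stayed. The Introduction says the study is meant to supply what is needed to refine the app and to design a later randomised trial. Reasons for non-use are direct input to that. The same section reports modest use (56%) in an earlier Dutch study, so non-use among participants is a realistic prospect.

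**Working it through.** **Step 1. Set the statements side by side.**

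| Place | Reasons for non-use named? | Who is asked |
|---|---|---|
| Introduction, objectives | Yes, alongside dropout | Not stated |
| Table 1 | Yes | Dropouts, on the natural reading |
| Outcomes and measures, text | No, dropout only | Discontinued participants, by email |
| Study procedures, follow-up survey | No | All participants |
| Quantitative analyses | No, dropout only | Not stated |

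The objective covers two events. No place in the article clearly puts the non-use questions to participants who stay.

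**Step 2. Reproduce the plan's own figure.** Sample size states: "a sample size of n=75 is deemed sufficient to obtain data of n=60 participants for analyses at follow-up, expecting a dropout rate of 20"%. Check: 60 / (1 − 0.20) = 75, which matches. Expected dropouts: 75 − 60 = 15.

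**Step 3. Illustrate the size.** The protocol gives no expected rate of non-use for this study. Carrying over the Dutch 56% use is an assumption, and the article does not define use there. It gives 44% non-use:

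- Expected non-users: 75 × 0.44 = 33.
- If non-use is equally common in dropouts and completers: 15 × 0.44 = 6.6 asked and 60 × 0.44 = 26.4 retained and unasked, which is 26.4 / 33 = 80% of non-users.
- If every dropout is a non-user: 15 asked and 33 − 15 = 18 retained and unasked, which is 18 / 33 = 55% of non-users.
- As a share of the 60 completers: 18 / 60 = 30% to 26.4 / 60 = 44%.

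**Step 4. Vary the assumed rate.** The low end puts as many non-users as possible among the 15 dropouts; the high end makes non-use unrelated to dropout.

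| Non-use | Non-users of 75 | Retained and unasked, low | Retained and unasked, high | Share of non-users missed |
|---|---|---|---|---|
| 20% | 15 | 15 − 15 = 0 | 60 × 0.20 = 12 | 0% to 80% |
| 30% | 22.5 | 22.5 − 15 = 7.5 | 60 × 0.30 = 18 | 33% to 80% |
| 44% | 33 | 18 | 26.4 | 55% to 80% |
| 50% | 37.5 | 37.5 − 15 = 22.5 | 60 × 0.50 = 30 | 60% to 80% |

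These counts assume that every dropout answers the email. Any non-response lowers the number of non-users heard from.

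**Step 5. Look for another route to retained non-users.** Under Study procedures, the focus group draws its 8 members from people who agree during follow-up to be contacted again. It aims for a spread of engagement if availability allows, so it may include some low users. Under Qualitative analyses it is described as a formative supplement, and its listed topics do not include reasons for non-use. Under Adverse events, participants can record problems in the app, which requires opening it, or contact the team on their own initiative. None of these yields a distribution of reasons among retained non-users.

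**The case against.** The best counter-argument is that the Table 1 row can be parsed differently. Its closing clause may qualify only leaving the study, with the non-use questions open to anyone. That fits the two-part row label and the two-part objective, and the row is marked at follow-up, a visit that dropouts miss by definition. The mark is weak evidence, because the app metadata row carries the same one.

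The other sections are also summaries that are visibly incomplete. The baseline list in Study procedures omits the risk-profile instruments that Table 1 marks at both visits, and the list in Quantitative analyses does not name usefulness, a key outcome. Their silence does not prove that a non-use item is absent from the full protocol or the survey.

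This stands as far as it goes. A reader might infer that the protocol definitely excludes retained non-users from the question; the wording does not establish that. But the alternative reading finds no positive support elsewhere in the article, and two sections narrow the outcome to dropout explicitly. Even if the authors meant the wider group, the statements do not agree and need reconciling.

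The focus group is a fair partial mitigation, since it is meant to produce suggestions for refinement. It remains a single group of 8.

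**Conclusion.** The concern holds in a limited form. The article sets an objective on reasons for non-use. On the most natural reading of Table 1, supported by the text of Outcomes and measures and by the Quantitative analyses, it does not collect those reasons from participants who stay in the study. It should be corrected before recruitment opens, planned for 1 November 2026.

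The size is uncertain. With 44% non-use, about 18 to 26 of 33 non-users would be retained and unasked, but that rate is a Dutch result and not a planning value for this trial. A reader might take 18 as a minimum. It is not: at 20% non-use the low end is 0.

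Two further inferences are tempting and go beyond the document. One is that the protocol names non-use as its main feasibility risk. It only reports the Dutch figure, and its stated limitations concern recruiting diverse participants and floor effects. The other is that refinement of the app will be misdirected. Incomplete reasons may mislead, but nothing in the article shows that they will.

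**What to change.** Reword Table 1, Study procedures, the text of Outcomes and measures, and Quantitative analyses so that they agree:

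1. Ask the standardised non-use questions in the 12-week online follow-up of every participant who reports not having used the app or having stopped. Trigger them with a self-report screening item and use app metadata as a check. Self-report is the safer trigger because, under Recruitment, the study ID is stored in the app only at first login, so someone who never logged in may leave no linked record.
2. Add these items to the usability and usefulness ratings for anyone who used the app, and do not substitute them. Dropping the ratings for people who stopped would remove disengaged users selectively and could flatter the usability results.
3. Keep the email to those who leave the study.
4. Report reasons for non-use and reasons for dropout separately, each with its denominator and the number responding.

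The cost is a few extra survey items for non-users and early stoppers, plus one screening item and one branch in a survey that is already planned. If the wider group was always intended, only the rewording and the separate reporting are needed.
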